**8-2 Exclusion Criteria**

(1) Intraepithelial carcinoma

(2) Stage IV

(3) The patient who underwent the sentinel node biopsy only

(4) The patient who underwent the total mastectomy and the simultaneous reconstruction surgery

(5) When the shoulder movement disorder derived from the other preoperative shoulder-related diseases exists.

(6) The patient with a breast cancer on the east side or the history of surgery on the axillaries

(7) The patient who is pregnant or breastfeeding

**8-3 The target enrollment number of subject and the grounds of estimation [28]**

This clinical trial is to evaluate the efficacy of Guardix SG, anti-adhesive agent composed of alginate and poloxamer in the range of motion of patient’s shoulder joint who is scheduled to undergo the modified radical mastectomy or breast preservation surgery and the axillary lymph node dissection.

According to the related literature, over 10 degree-difference in the ROM considered to be significant clinically [17] and over 10 degree-difference between the experimental group and the control in the ROM is considered to be significant. Therefore, we estimate the 192 persons(total) as a target enrollment number by assigning 96 subjects for each group in consideration of the drop-out rate of 10% under the precision degree of 0.025, power of 90%, and standard deviation of 10 [25] using Pass software.

* The rationale for our study is as follows.

**H_0_ : D ≤ 10 H_1_ : D〉10 (D=Experimental group(EG) ROM Mean – Control group(CG) ROM Mean)**

* Basis of Calculation: Assumptions for estimating the effective subject number.

① Significance level α = 0.025

② The EG estimation number is 1 time that of CG.

③ Type 2 error (β) is 0.1, and statistical power 90% is maintained.

④ The difference in the average value between two groups: 10 degree.

[figure not shown]

[figure not shown]

[figure not shown]

| Power | N1/N2 | Equivalence Margin  (E) | Actual  Difference  (D) | Significance  Level  (Alpha) | Beta | Standard  Deviation1  (SD1) | Standard  Deviation2  (SD2) |
| --- | --- | --- | --- | --- | --- | --- | --- |
| 0.90022 | 23/23 | 5 | 10 | 0.025 | 0.09978 | 5 | 5 |
| 0.80044 | 17/17 | 5 | 10 | 0.025 | 0.19956 | 5 | 5 |
| 0.90004 | 86/86 | 5 | 10 | 0.025 | 0.09996 | 10 | 10 |
| 0.80003 | 64/64 | 5 | 10 | 0.025 | 0.19997 | 10 | 10 |
| 0.90022 | 191/191 | 5 | 10 | 0.025 | 0.09978 | 15 | 15 |
| 0.80044 | 143/143 | 5 | 10 | 0.025 | 0.19956 | 15 | 15 |
| 0.91250 | 23/23 | 10 | 15 | 0.025 | 0.08750 | 5 | 5 |
| 0.80704 | 17/17 | 10 | 15 | 0.025 | 0.19296 | 5 | 5 |
| 0.90323 | 86/86 | 10 | 15 | 0.025 | 0.09677 | 10 | 10 |
| 0.80146 | 64/64 | 10 | 15 | 0.025 | 0.19854 | 10 | 10 |
| 0.90022 | 191/191 | 10 | 15 | 0.025 | 0.09978 | 15 | 15 |
| 0.80044 | 143/143 | 10 | 15 | 0.025 | 0.19956 | 15 | 15 |

Suppose that the 10% subject is dropped out in the middle of trial, the necessary total subject is 192 persons composing of 96 persons for the experimental group and 96 persons for the control.

| Target subject number | EG | CG | In total subject number |
| --- | --- | --- | --- |
| Subject number for final efficacy evaluation | 86 | 86 | 172 |
| Subject number in consideration of drop-out rate (10%) | 96 | 96 | 192 |

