**15. Evaluation Methods and Interpretation Methods**

**15-1 Assessment of Efficacy Methods and Interpretation**

(1) Evaluate using the questionnaire prepared by the researcher and subject

(2) Primary Efficacy Criteria Analysis

The each range of motion’s angle is measured at 4 states of ROM (range of motion) using the universal full-circle manual goniometer on the preoperative day and the 3th month, the 6th month, and the 12th month following the surgery. The measured value is used to analyze the significance at each ROM’s state comparatively by performing the one side and two sample student T-test with the difference and the variance between two groups measured at each period (from preoperative day to the 3th month, the 6th month, and the 12th month following the surgery). When there is over 10 degree differences between two groups (that is the lowest value of confidential interval is over 10), the investigational group is superior to the control. (The over 10 degrees difference of two group is considered to be significant clinically when comparing it).

(3) Secondary Efficacy Criteria Analysis

- Evaluation on the upper limbs’ locomotive capacity (questionnaire – DASH (disability of the arm, shoulder and hand))

The score of DASH questionnaire consist of 30 questions is calculated based on the items filled by the subject.

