**15-3 Statistical Analysis**

(1) Methods: One side, Two sample student t-test, Chi-square test, Fisher’s exact test

(2) Main analysis: ITT analysis

(3) Additional analysis: PP analysis

(4) Statistical power: 80%

* When performing the statistics for effectiveness evaluation, the information of subject who stopped to participate in or was dropped out from clinical trial is excluded from the compliance group (per protocol group) and is dealt as a missing value when the subject is assigned to the analysis group according to assignment table.

(5) General Principals of statistical analyses

The subject data of this study were analyzed through ITT (Intention to Treat) analysis and PP (Per Protocol) analysis.

In the ITT analysis, all the data obtained from the subjects who used the investigational device at least once after they were randomly assigned to the group were used. The above-mentioned subject’s information is excluded from the analysis for primary and secondary the missing value at the primary and secondary is discovered.

In the PP analysis, ITT analysis was data obtained from the subjects who completed the clinical trial according to the protocol were included. And the above-mentioned subject’s safety endpoint shall be included in ITT group. The value of subject which is out of clinical trial’s policy critically and may affect the efficacy evaluation (Exclusion criteria 2. The subject who is diagnosed as a breast cancer, absent on visit 1 and 2(each), assigned to the incorrect group, and experiences the severe adverse events during the clinical trial) will be included in the ITT group analysis with being excluded from the PP group analysis.

The efficacy evaluation was conducted using The efficacy evaluation was conducted using the ITT and PP analysis as a main method, while the PP analysis was used as an auxiliary method when the analysis results were inconsistent. The results of both analyses were compared. Demographical evaluation and safety evaluation were basically analyzed through the ITT analysis.

(6) Demographical Data

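### Item 4 of the sample-size assumptions puts the difference at 10 degrees, the null boundary; 86 per arm gives 90% power only at a true difference of 15 degrees, which the text never assumes or justifies

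*Protocol*

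**What the plan says.** - **Hypothesis (8-3).** H0: D ≤ 10 against H1: D > 10, where D is the mean range of motion in the experimental group minus that in the control group.
- **Success rule (15-1 (2)).** The device is superior when the between-group difference is over 10 degrees, explained as "that is the lowest value of confidential interval is over 10". The test comes from "performing the one side and two sample student T-test".
- **Listed assumptions (8-3).** "Significance level α = 0.025"; equal allocation; "Type 2 error (β) is 0.1, and statistical power 90% is maintained"; and, as item 4, "The difference in the average value between two groups: 10 degree". The introductory text gives 96 per group after 10% drop-out, "under the precision degree of 0.025, power of 90%, and standard deviation of 10".
- **Power table (8-3).** Two rows have SD 10, about 90% power and 86 per arm. One has margin 5 and actual difference 10: "0.90004 | 86/86 | 5 | 10 | 0.025 | 0.09996 | 10 | 10". The other has margin 10 and actual difference 15, with printed power 0.90323. The text does not say which row was used.
- **Analysis section (15-3 (4)).** "Statistical power: 80" (per cent), where 8-3 says 90%.

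**The concern.** The margin is stated twice, consistently, as 10 degrees. The only difference named in the list of assumptions is also 10 degrees. If the true difference equals the margin, the trial is on the edge of its null hypothesis and its chance of success is the type I error rate, whatever the sample size. Items 3 and 4 of the list therefore cannot both hold under the stated H0.

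What is at stake is the reading of the primary result. Someone who takes items 3 and 4 together would believe the trial has a 90% chance of success if the device adds 10 degrees. Under the stated rule, that chance is reached only at 15 degrees. A failed trial could then be taken as evidence against a benefit of 12 or 13 degrees, which the design is poorly placed to detect. The two table rows also leave room for a dispute over whether the margin is 5 or 10. If that were settled after the data were seen, the success threshold would move by 5 degrees.

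**Working it through.** **Inputs.** From 8-3: SD 10 in both groups, alpha 0.025, 1:1 allocation, 86 evaluable per arm, 10% drop-out, margin 10 (H0). From 15-1: one-sided two-sample t-test, success if the lower limit is over 10. I take that limit to correspond to one-sided 0.025, and I treat a single comparison (one motion at one visit).

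**1. Reproduce the plan's figures.** Power depends on D and the margin E only through D − E. With D − E = 5, the normal approximation gives

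n = 2 × 10² × (1.960 + 1.282)² / 5² ≈ 84.1, so 85 per arm.

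For the t-test, the standard error is 10 × √(2/86) = 1.525, the noncentrality is 5 / 1.525 = 3.279 and df = 170. Power is 0.90323, which is the printed value in the margin 10, difference 15 row to every digit. Drop-out: 86 / 0.9 = 95.6, so 96 per arm. Both 86 and 96 stand.

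The margin 5, difference 10 row has the same D − E and so should show the same power. It prints 0.90004, an immaterial gap.

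**2. Match the two rows to the text.**

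| Row (SD 10, 86/86) | Agrees with H0 and 15-1? | Agrees with item 4? |
| --- | --- | --- |
| Margin 5, difference 10 | No | Yes |
| Margin 10, difference 15 | Yes | No |

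Neither row agrees with everything in the text. Testing against a null of zero does not explain 86 either: at D = 10 that would need only 22 per arm.

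**3. Power under the stated hypothesis and rule** (margin 10, SD 10, one-sided 0.025, noncentral t):

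| True difference | 86 per arm | 96 per arm |
| --- | --- | --- |
| 10 | 0.025 | 0.025 |
| 11 | 0.095 | 0.102 |
| 12 | 0.256 | 0.281 |
| 13 | 0.498 | 0.543 |
| 14 | 0.742 | 0.787 |
| 15 | 0.903 | 0.931 |

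The second column shows that full retention does not change the picture.

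**4. Observed difference needed.** 10 + 1.974 × 1.525 = 13.01 degrees.

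**5. Cost of 90% power at smaller differences** (normal approximation, margin 10): 234 per arm at D = 13, 526 at D = 12 and 2,102 at D = 11. At D = 10 no finite n suffices.

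**The case against.** The strongest reply is that item 4 is a mislabelled margin. Section 8-3 uses 10 degrees only as the threshold of clinical importance. Item 4 does not call it a true or expected difference, and the images that follow it, which are not reproduced in the text available, may bear on how it was used. On that reading, H0, the success rule, alpha, SD, n and the margin 10, difference 15 row all agree, and the gap is one of statement and justification. This may well be what happened. It does not remove the point: item 4 stands under the assumptions for the calculation, and 15 degrees is neither stated nor defended anywhere in the text.

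Three stronger readings are tempting, and the documents do not support them:

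- **That the trial's power simply is 2.5%.** This holds only at a true difference of 10. The protocol's own table contains a row that fits H0 and the success rule and gives 0.903 at 15.
- **That a device delivering the clinically important difference would wrongly fail 97.5% of the time.** Sections 8-3 and 15-1 call a difference over 10 degrees important, and H0 includes exactly 10. A 2.5% success rate there is the intended type I error. The fair concern is low power just above 10.
- **That the sample size is miscalculated.** Both 86 and 96 reproduce.

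The 80% entry in 15-3 is a smaller, separate slip. The target number is tied explicitly to 90%.

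**Conclusion.** The point holds as an inconsistency between the listed assumption and the stated hypothesis. The 90% power in 8-3 does not belong to the listed set of assumptions: with margin 10 and the 10-degree difference of item 4, power is 2.5% at any n. For the stated hypothesis and 86 per arm, 90% belongs to a true difference of 15 degrees. Halfway between the margin and that value the power is poor (37% at 12.5 degrees), and an observed difference of about 13.0 degrees is needed to succeed.

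These figures assume SD 10, a lower limit at one-sided 0.025, and one comparison taken alone. They do not show that the trial is too small for its purpose. That depends on whether 15 degrees is a credible effect, and the protocol gives no basis for judging it. Section 15-3 (4) adds a second, conflicting power figure.

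**What to change.** With n unchanged:

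1. Keep H0 in 8-3 and the success rule in 15-1 at 10 degrees.
2. Restate item 4 as two separate inputs, a margin of 10 degrees and an assumed true difference of 15 degrees. Name the table row used and justify the 15.
3. State that power is 90% only at 15 degrees, and report the power between 10 and 15 (about 10% at 11, 26% at 12, 50% at 13 and 74% at 14).
4. Replace the 80% in 15-3 (4) with the single figure used in 8-3.

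This costs an amendment to the text of 8-3 and 15-3 and no extra subjects. The stated power will look less favourable, and a justification for 15 degrees has to be found.

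If the sponsor in fact intended margin 5 with a difference of 10, that is more than a change of wording. It halves the margin in the primary hypothesis and the decision rule. It would have to be justified against the 10-degree clinical threshold in 8-3 and 15-1, and made before unblinding.

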**9. Period of Clinical Trial**

30 months subsequent to the approval date from IRB of MFDS

* Subject enrollment period: 12 months

* Period for observation study and clinical trial: 12 months

* Statistic processing period: 4 months

* Result report preparation period: 2 months

**10. Methods of Clinical Trial**

**10.1 Investigational device**

(1) Investigational device

1) Product-License No.: 09-826 (Code: BM2102JO)

2) Product name: Deep-cavity wound dressing

3) Model name: GUARDIX SG

4) General name: Anti-adhesion agent.(solution)

(2) Raw materials

Poloxamer, Sodium alginate

(3) Shape·structure and measurements

1) Shape·structure

GUARDIX SG solution is a sterilized non-febrile, colorless, transparent viscous poloxamer/sodium alginate mixture solution. It provides a temporary viscous/lubricative coating on the wound surface after surgery. It is contained in a pre-filled syringe, and packed under a sterilized environment for use.

[figure not shown]

[figure not shown]
A) Picture of exterior

B) Explanation of exterior

① Catheter tube: Guardix SG to flow toward the surface of patient’s wound subsequent to the surgery.

② Stopper: To seal the syringe in order for the liquid not to leak.

③ Syringe: To contain the liquid of Guardix SG.

④ Finger grip: To grip the finger

2) Size and weight

A) Exterior size

The solution of Guardix SG (3ml and 6ml) is pre-filled within the syringe(material: cycloolefine copolymer, capacity: 5ml and 10ml) and the syringe’s tip closed with the lid is packaged within the container which has a polyester fixer. The catheter (material: Polyethylene terephthalate (Teflon)) which guides the injected liquid of solution is packaged with the Tyvek connected to the package.

B) Weight: 3ml, 6ml

**10.2 Comparator device**

The Comparator device referred as an inactive control isn’t used in this clinical trial.

[Currently, it is uncommon to apply the anti-adhesive agent onto the surgical site of patient who underwent the modified radical mastectomy or breast preservation surgery and the axillary lymph node dissection and it is safe to apply nothing to the surgical site. Therefore, we couldn’t find the reference medical device and didn’t assigned any medical device as the control.]

**10.3 Methods of Clinical Trial**

(1) Clinical Trial Design

The eligibility evaluation is conducted with the subject who underwent the modified radical mastectomy or breast preservation surgery and the axillary lymph node dissection at Asan medical center and signed at the consent form voluntarily subsequent to the screening test. The subject who isn’t included in the exclusion criteria visits the hospital on the operation day and undergoes the modified radical mastectomy or breast preservation surgery and the axillary lymph node dissection. Then, the subject is assigned to the investigational group or control according to the random assignment slip.

 EG: Guardix SG

 CG: Not applicable

That means the investigational device will be or won’t be applied onto the surgical site of subject depending on her group. Since the investigational device is applied inside of subject in the middle of surgery under anesthetic, the subject is unaware of treatment’s detail.

The related tests will be performed on the 7th, 3, 6 and 12 months subsequent to the surgery. In addition, the double-blind policy is maintained since the application of investigational device is performed by the expert who has a medical expertise and technique on the surgery and the application of investigational device, and the evaluator couldn’t know about the rule of random assignment and the allocation of subject to the group since the evaluator isn’t involved to the application of investigational device.

(2) Random Assignment of Subjects

In this clinical trial, random assignment was used to reduce bias that could be involved in the assignment of EG and CG, and to enhance the effects of comparison. To compare the precise difference in the range of motion of patient who underwent the partial mastectomy or total mastectomy, the subjects are assigned to each group randomly in similar proportion.

Our random assignment method is the block random assignment performed after generating random numbers (upto 4 places of decimals) for each subject using Excel’s random function (RAND). The sealed assignment slip is distributed to the subject. The sponsor of clinical trial provides the blinded slip which the investigational group or control is written down according to the randomly assigned subject table.

Subject numbers were given by each clinical trial institution, and the institution assigned a screening number to each subject who signed the written consent and completed the screening test. Upon completion of the screening process, and if a subject was recognized to be appropriate for this study, a random assignment number was given in sequence, then treated with the investigational device.

The screening number as well as the random assignment number of a dropout subject was also dropped out. A new subject must be provided with a new subject screening number and random assignment number.

(3) Code Breaking

The blindness must not be disclosed during the clinical trial period in any case. The blindness can only be disclosed if the subjects are in emergency situation, and the group they belong to is absolutely required to be identified. In this case, the blindness can be disclosed according to the appropriate process, and details must be recorded in written documents.

(4) The method of surgery and the application method of medical device

Subsequent to surgery, the 3ml(injection volume) of Guardix SG is applied to the subject who underwent the modified radical mastectomy or breast preservation surgery and the axillary lymph node dissection, the standard surgery method to treat the breast cancer.

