**6-2. Background**

The various adverse events on the upper limbs such as the pain on the arm, the muscle weakness, the lymphedema, hypofunction of shoulder joint, and etc. occur following the breast cancer surgery. The shrinkage in the range of shoulder joint’s motion and the muscle weakness lead to the reduction in activities’ scope of daily living and the decline the quality of life [2-6]. Therefore, the treatment and effort to prevent the complication which occurs especially when the axillary lymph node dissection is performed is needed. Koostra et al. reported the complication (such as lymphedema, the range of shoulder joint’s motion, muscular strength, the exercise of upper limbs, and etc.) occurrence rate of patients who underwent the surgery on the sentinel node is lower than it of patients who underwent the axillary lymph node dissection in terms of statistical significance found at prospective studies. The significant factor related to the reduction in the range of shoulder joint’s motion affects the treatment method and the recovery period [1].

The occurrence rate of pectoralis tightness and the reducing degree in the range of shoulder joint’s motion of patients who underwent the mastectomy are higher than those of patients who underwent the breast preservation surgery. The quality of radiotherapy subsequent to the surgery also affects the occurrence rate of above-mentioned complications. The reducing degree on the range of shoulder joint’s motion is the largest within 12 months subsequent to the surgery and its reducing degree is small since that time [3-6].

Since the adhesion of surgical site which can occurs after the total mastectomy causes the reduction in the range of shoulder joint’s motion and the pain, the measure for reducing the above-mentioned symptoms significantly is needed by developing the method to prevent the adhesion. The fact that the application of HA-CMC onto the surface of pectoral muscle and serratus anterior muscle, the treatment for preventing the adhesion followed by the surgery, widened the range of shoulder joint’s motion of breast cancer patients and reduce their pain is discovered in the previous study on HA-CMC [17]. In addition, the other studies on HA-CMC showed the range of joint’s motion is widened after the application of HA-CMC which lessened the adhesion degree [21].

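### Balance by surgery type is stated as an aim, but no stratification factor is named and the primary t-test is unadjusted, so the aim is not secured and some precision is forgone

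*Protocol*

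**What the plan says.** **Balance aim.** Protocol section 10.3 (2) links the comparison of motion in patients "who underwent the partial mastectomy or total mastectomy, the subjects are assigned to each group randomly in similar proportion".

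**Method.** The next paragraph gives the procedure: "Our random assignment method is the block random assignment performed after generating random numbers" with the Excel random function, followed by sealed slips made up from an allocation table. It names no stratum, no block size and no separate list by type of operation. After screening, "a random assignment number was given in sequence".

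**Prognostic factor.** On pectoralis tightness and loss of shoulder motion, section 6-2 says that the figures "of patients who underwent the mastectomy are higher than those of patients who underwent the breast preservation surgery". It gives the direction but no size in degrees.

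**Analysis.** Section 15-1 (2) fixes the primary analysis as "performing the one side and two sample student T-test with the difference and the variance between two groups measured at each period", where the periods run from the preoperative day to 3, 6 and 12 months. Section 15-3 (1) lists the methods as "One side, Two sample student t-test, Chi-square test" and Fisher's exact test. Neither section includes a covariate or a stratified method.

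**Timing of assignment.** Section 10.3 (1) places assignment after the operation. Section 10.3 (2) gives the random number once screening is complete, and the visit schedule puts screening before surgery.

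**The concern.** Blocks without strata keep the group totals equal. They do nothing to keep the mix of operations equal within those totals. The protocol therefore states an aim that its described procedure does not deliver, for a factor that it calls prognostic for the primary endpoint.

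The analysis does not make up for this. Variation in motion between surgery types stays in the error term of the t-test and widens the confidence interval, and section 15-1 (2) decides superiority on the lower limit of that interval. The wording also leaves whoever prepares the slips unable to tell whether one list or two are wanted.

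**Working it through.** **Inputs from the protocol** (sections 8-3 and 15-1): one-sided alpha 0.025, SD 10 degrees, 1:1 allocation, 86 evaluable and 96 enrolled per group. The 86 comes from the sample-size row with margin 5 and difference 10, so the distance from the margin is 5 degrees.

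**Assumptions, not in the protocol:** share p of patients with mastectomy, difference g in mean change between surgery types, and blocks of 4.

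**1. The plan's own figure.** The exact t calculation for a 5-degree distance and SD 10 gives power 0.8999 with 85 per group and 0.9032 with 86, so 86 is reproduced. For dropout, 86 / 0.90 = 95.6, which rounds up to 96.

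**2. Imbalance without stratification.** The SD of the between-group difference in mastectomy share is √(2p(1−p)/n). With n = 96 and p = 0.5 this is √(0.5/96) = 0.072, or 7.2 points. Simulated trials with 192 patients in blocks of 4 give:

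| p | SD, points | Trials with a gap above 10 points |
|---|---|---|
| 0.5 | 7.2 | about 17% |
| 0.3 or 0.7 | 6.6 to 6.7 | about 13% to 14% |

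At p = 0.5 the 95th percentile of the gap is 14.6 points. With stratified blocks of 4, the two groups could differ by at most 2 patients per stratum.

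**3. Precision, taking SD 10 as the total SD.** The variance between types is p(1−p)g², so the residual SD after adjustment is √(100 − p(1−p)g²). With p = 0.5, 86 per group and a 5-degree distance (exact t; the degree of freedom lost to the covariate is ignored):

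| g, degrees | Variance removed | Residual SD | Power |
|---|---|---|---|
| no adjustment | – | 10.00 | 90.3% |
| 3 | 2.25% | 9.89 | 90.9% |
| 5 | 6.25% | 9.68 | 92.0% |
| 10 | 25% | 8.66 | 96.4% |

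At p = 0.3 the adjusted powers are 90.8%, 91.8% and 95.6%.

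**4. If SD 10 is instead the SD within a surgery type.** The total SD is then √(100 + p(1−p)g²): 10.11, 10.31 and 11.18 at p = 0.5. Unadjusted power falls to 89.7%, 88.5% and 83.0%.

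**5. Chance imbalance and lost precision are one cost.** The unadjusted variance of the contrast is 2 × 100/86 = 2.33 (SE 1.53 degrees). With g = 10 and p = 0.5, imbalance in surgery type contributes 10² × 0.5/86 = 0.58, which is 25% of 2.33. This is the same 25% as in step 3, so the unadjusted standard error already contains it.

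**6. Preoperative motion.** With equal variances before and after surgery and correlation ρ, the variance under ANCOVA relative to a change score is (1−ρ²)/(2(1−ρ)) = (1+ρ)/2: 0.65, 0.75 and 0.85 for ρ = 0.3, 0.5 and 0.7. The protocol gives no ρ, and the power figures above do not use this gain.

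**The case against.** **A reader might infer that the protocol chose a single unstratified list.** It does not say so. The balance sentence may be a poorly worded statement of stratification, or of plain 1:1 allocation, and issuing numbers in sequence is possible within strata too. What stands is that no stratification factor is named. Each reading calls for a correction: if stratification was meant, the text does not instruct it and the unadjusted test would be conservative; if not, the balance statement has no support.

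**A reader might infer that the primary result would be biased.** It would not. Under unstratified randomisation the t-test has no average bias and no inflated type I error. A 14.6-point gap with g = 10 would move one trial's contrast by about 1.5 degrees, but step 5 shows that the standard error already allows for this.

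**The loss of precision may be slight.** This largely stands. If SD 10 is the total SD, the planned power is kept and only a possible gain is forgone: 0.6 to 1.7 points at 3 to 5 degrees. The 6-point gain needs a 10-degree difference between types, as large as the difference that section 8-3 calls clinically important.

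**The power figures do not describe the stated hypothesis.** Correct. Section 8-3 also states H0 as D ≤ 10 with an expected difference of 10. Power there is 2.5% whatever the covariates. That is a separate and larger conflict, and it does not remove this one.

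**Surgery type may not be known at assignment.** The protocol conflicts with itself on timing, so this cannot be taken as settled.

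**Conclusion.** The concern holds in a limited form. The protocol states a balance aim by surgery type, treats the factor as prognostic, names nothing in the randomisation that would secure the balance, and fixes a primary test that ignores the factor. The consequences are an unsecured aim and forgone precision; the primary test stays valid.

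The figure of about 17% of trials with a gap above 10 points assumes an unstratified list and half the patients with mastectomy. The rise in power from about 90% to 91%, 92% or 96% assumes a total SD of 10, the 5-degree distance from the margin and surgery-type differences of 3, 5 or 10 degrees, none of which the protocol reports. At the lower two values the gain is small. The case for the change rests on the mismatch in the text and the low cost of repair more than on the power gained.

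**What to change.** 1. In section 10.3 (2), name surgery type (breast-conserving surgery or mastectomy) as the stratification factor and prepare a separate permuted-block list for each type.
2. Reconcile sections 10.3 (1) and 10.3 (2) on whether assignment follows screening or the operation, and say accordingly whether the stratum is the planned or the performed operation.
3. In sections 15-1 (2) and 15-3 (1), replace the plain t-test for the primary endpoint with a linear model (ANCOVA) with treatment, surgery type and preoperative range of motion. The confidence limit for the treatment effect then comes from that model.

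The cost is two sets of slips instead of one and two covariates. No extra patients or measurements are needed: section 11-1 already records the name of the operation and preoperative motion. If stratification is not wanted, the balance statement should be removed; the adjusted model is still worth having.
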